Given that this study considers more than one measurement (repeated measures) over time, this information should be considered as correlated within-subjects. Therefore, to analyze variables associated with the PICS-F impairments over time, panel or longitudinal analysis will be used. First, graphical methods, such as panel line plots, will be used to visualize the trend and variation between and within-subjects over time. This analysis will be useful for determining some important covariates and the regression models to be included and applied afterward. Second, the strength of outcome correlation should be defined to decide the regression methods. In this scenario, and considering the nature of the outcome, generalized linear mixed models (GLMM) will be used. Contextual factors (family member and patient features) of each subject will be considered fixed effects, but random effects will be included because it is expected that the outcome in each time and for each subject will vary. Given that the outcome is measured as a dichotomous variable, the family will be binomial, and the link function is expected to be logit. Then, the model will be built starting with a large model and trimming it down according to statistical significance but also based on the proposed theoretical model (CSM). The initial models proposed for this study are presented in Table 1.

If family satisfaction (FS) or caregiver burden (CB) is associated with any of PICS-F impairments at T3 and/or T4, GLMM with and without the selected secondary stressor will be fitted to analyze the extent of this association. First, FS measured at T1 will be added to models 1-4 while the FS measure at T2 will be included in models 5-8. Similarly, CB measured at T3 will be included in models 9-20 while the T4 measure of CB will be added to models 17-20. The original model without a secondary stressor will be contrasted

with the same model plus the secondary stressor (either FS or CB). Scores such as Akaike Criterion and likelihood ratio tests will be performed and residual plots will be obtained. Also, 95% confidence intervals will be reported and a  $p$ -value  $< .05$  will be considered statistically significant. All statistical analyses will be conducted in R, using the applicable packages.

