a Models will be tested with T3 and T4 dependent variables separately. SOFA: sequential organ failure assessment score; ICU: intensive care unit; BI: Barthel index; MHA: mental health antecedents; LOS = length of stay; PHQ-4: patient health questionnaire; IES-6: impact of event scale; mMOS-SSS: modified medical outcomes study social support scale; BRCS: brief resilience coping scale; SF-36 VT: short-form health survey, vitality subscale; MEFO: memory, fluency, and orientation test.

**Sample Size:** The study sample size will consider the following values: alpha = 5%, a beta = 80%, and precision of estimate = 5%. Because of the lack of studies utilizing the same questionnaires to establish PICS-F incidence, a 20% incidence of PTSD symptoms reported in a study utilizing an IES-6  $\geq 1.75$  will be utilized. Based on these parameters, the calculation of the sample size is obtained by the following formula:  $[Z^2 \times P \times (1-P)]/e^2$  where  $Z$  is the value from standard normal distribution associated with a particular confidence interval (CI), which in this case is set at 95%,  $P$  is the expected true proportion in the population, and  $e$  is the desire precision level. Consequently, the initial sample size is 247 RFM.

This sample size will be adjusted for a finite population. In this study, the finite population will be 600 since it represents the average 2019-2020 number of ICU admissions ( $\pm 550$ ) plus a 10% of projected increase during 2023. Data of 2021 will not be considered since it was heavily influenced by the COVID-19 pandemic waves of ICU admissions and it is not likely to be representative of 2023. Then, the adjusted sample size is obtained using the following formula:  $(\text{finite population} \times \text{initial sample size}) / (\text{finite population} + \text{initial sample size})$ . Thus, the adjusted sample size will be 175 RFM. However, considering the attrition rates reported in the literature, 40% of losses are contemplated leaving 292 RFM as the final adjusted sample size.

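### The random-effects models in Table 1 are each fitted to a single visit, so the subject variance is practically inestimable and no listed regression analyses the repeated outcomes jointly

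*Protocol*

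**What the plan says.** The Protocol, Methods, Statistical analyses, says of the repeated measures that "this information should be considered as correlated within-subjects". It continues that "to analyze variables associated with the PICS-F impairments over time, panel or longitudinal analysis will be used", and that "generalized linear mixed models (GLMM) will be used". The reason given for the random part is that "random effects will be included because it is expected that the outcome in each time and for each subject will vary". On distribution and link, "the family will be binomial, and the link function is expected to be logit". The section then points to the concrete models: "The initial models proposed for this study are presented in Table 1".

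Table 1 lists 20 models. Models 1-8 use T1 or T2 predictors. Their outcome header names T3 and T4 and carries footnote a: "Models will be tested with T 3 and T 4 dependent variables separately". The outcome header is T3 for models 9-16 and T4 for models 17-20. No row combines the two visits and none lists visit or time as a term.

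The comparisons with and without family satisfaction or caregiver burden, by Akaike criterion and likelihood-ratio test, use these same models.

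**The concern.** A subject random intercept describes how outcomes from the same person resemble each other, so it needs at least two outcomes per person in the same fit. The text promises that structure and the table removes it. Nothing else could carry a random effect: the study has one ICU, and one representative relative is enrolled per patient.

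Two things are at stake. First, a logistic mixed model reports subject-specific odds ratios, whose size depends on the random-intercept SD. If the data cannot determine that SD, the reported odds ratios and 95% confidence intervals rest on an arbitrary value. Second, the within-subject analysis over time that the section describes is not carried out by any listed regression model. Any difference between T3 and T4 would be read informally across two separate fits.

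**Working it through.** **Step 1. Outcomes per relative in each fit.**

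| Models in Table 1 | Outcome visit in one fit | Binary outcomes per relative |
|---|---|---|
| 1-8 (footnote a) | T3 or T4, separately | 1 |
| 9-16 (T3 header) | T3 | 1 |
| 17-20 (T4 header) | T4 | 1 |

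Rows 13-16 are irregular as printed. Rows 13-15 mark two outcome columns, row 16 marks only PHQ-4, and PHQ-4 appears as both predictor and outcome. This may come from reading the table out of the PDF, or the rows may be meant as T3 predictors of T4 outcomes. Either way each fit uses one visit.

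**Step 2. The plan's own sample size**, used here as the number of relatives analysed.
- Precision formula: 1.96² × 0.20 × 0.80 / 0.05² = 245.9, or 246 (the Protocol states 247).
- Finite population: 600 × 247 / (600 + 247) = 174.97, or 175, as stated.
- Losses of 40%: 175 / 0.60 = 291.7, or 292, as stated.

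These figures rest on the precision of one proportion and do not involve the mixed models.

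**Step 3. What one outcome per relative says about the variance.** For subject i, logit P(Y=1) = a + b·x + u, with u normal and SD sigma. The likelihood was integrated over u by 60-point quadrature and maximised over a and b at each fixed sigma. Assumptions not taken from the Protocol: 175 relatives, true sigma 1.5, one standard-normal predictor with b = 0.7, a = -1.85, 60 simulated data sets.

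| sigma | 0 | 0.5 | 1 | 1.5 | 2 | 3 | 4 | 5 |
|---|---|---|---|---|---|---|---|---|
| Median drop in 2 × log-likelihood, one visit | 0.00 | 0.05 | 0.06 | 0.05 | 0.04 | 0.02 | 0.01 | 0.00 |
| Median log-odds ratio, one visit | 0.48 | 0.50 | 0.56 | 0.65 | 0.75 | 0.98 | 1.23 | 1.49 |
| Median drop in 2 × log-likelihood, T3 and T4 stacked | 8.90 | 6.07 | 1.63 | 0.00 | 1.62 | 10.06 | 20.93 | 31.57 |

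With one visit, every sigma from 0 to 5 lay within the 3.84 cutoff in all 60 data sets. Within a data set the range of 2 × log-likelihood had median 0.12 and 95th percentile 0.45. Sigma = 0 was never rejected. With both visits stacked, the profile peaked at the true 1.5 and sigma = 0 was rejected in 90% of data sets (cutoff 2.71).

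**Step 4. What moves and what does not.** The subject-specific odds ratio goes from exp(0.48) = 1.62 at sigma 0 to exp(1.49) = 4.44 at sigma 5. The population-averaged effect is approximately b / √(1 + 0.346·sigma²), where 0.346 = (16√3/15π)². At sigma 5 this gives 1.49 / √(1 + 0.346 × 25) = 1.49 / 3.11 = 0.48, the value at sigma 0. The drift is thus a change of scale that one outcome per person cannot detect.

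**Step 5. The with/without comparisons.** In a separate set of 60 simulated data sets (same n, sigma and intercept; two predictors with log-odds 0.7 and 0.4), the median likelihood-ratio statistic for adding the second predictor was 1.81, 1.80, 1.81, 1.81 and 1.82 at sigma 0, 1, 2, 3 and 5. The median range within a data set was 0.09, and the 5% decision changed in 1 of 60. The first predictor's population-averaged odds ratio stayed at 1.60-1.61 while its subject-specific odds ratio rose from 1.61 to 4.42.

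**The case against.** The strongest reply is that little of substance is lost. The research questions ask for associations at three and at six months, which visit-specific models answer. Models 1-8 are prospective, because T1 and T2 predictors precede the outcomes. No research question, aim or hypothesis asks explicitly for change from T3 to T4. Table 1 is described as a starting set, panel line plots are planned, and the strength of outcome correlation is to be considered when choosing the method. If the software returns a variance of zero, the fit is simply ordinary logistic regression. All of this stands, and it limits the point.

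It does not remove the contradiction. Trimming predictors from the listed models does not add a second visit, and a zero variance is only one value that a flat likelihood allows. Prospective prediction is also not a reason for a subject random effect.

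A reader might go further and infer that the tests of Hypothesis 3 are invalid. They are not: a likelihood flat in sigma leaves likelihood-ratio and AIC comparisons almost unchanged (Step 5). Nor does the spread of odds ratios mean that the data cannot tell a weak association from a strong one. Those are subject-specific odds ratios at imposed values of sigma, and the population-averaged association is stable. It would also be too strong to say that the longitudinal aim is not addressed at all.

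**Conclusion.** The contradiction holds. The Protocol motivates random effects by within-subject correlation, yet each model it lists uses one visit and one binary outcome per relative. The random-intercept variance is formally tied to the data through the slight difference between the logistic-normal and logistic curves, but it is inestimable in practice. Subject-specific odds ratios and their confidence intervals would follow whatever variance is returned, and no listed regression carries out the described analysis over time.

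The particular odds ratios depend on the simulation assumptions. The flat profile follows from having one outcome per relative. Incidence estimates, the sample size and visit-specific association tests are not materially affected. This should be fixed before analysis, so that the choice of model does not depend on which fit converges. It does not undermine the study.

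**What to change.** - **Models 1-8:** replace footnote a with one mixed model per outcome that stacks T3 and T4 (two rows per relative). Include a subject random intercept, visit, and visit-by-predictor terms for the key predictors, so that both visit-specific effects come from one model.
- **Models 9-20:** first reconcile the outcome columns. As printed, models 9-12 point to PHQ-4, SF-36 VT, MEFO and MEFO, and models 17-20 to PHQ-4, IES-6, SF-36 VT and MEFO. State what models 13-16 are for. Then stack the matching T3 and T4 outcomes with time-varying predictors.
- **Any model kept at a single visit:** call it ordinary logistic regression and drop the random effect.

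The cost is wording in the Statistical analyses section and in Table 1. The data and software stay the same, stacking means fewer fits, and relatives seen at only one of the two visits still contribute to a stacked model.

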## PICS-F Psychological Impairments

Within PICS-F impairments, psychological sequelae are the most investigated and have been associated with the use of psychotropic medication in up to 32% of family members who start these medications after ICU admission and 40% seeking healthcare professionals for emotional problems. In a systematic review including 22 studies published until 2018, family members of ICU survivors reported a variable incidence of anxiety (4%-94%), depressive (2%-80%), and PTSD (3%-62%) symptoms after ICU discharge. The only published study conducted in Chile showed an incidence of 22.9% of PTSD symptoms 2 months after hospital discharge, which resembles subjects who endured the 2010 earthquake in Chile.

Recently published studies have shown similar results. In a single-center study, family members reported 30.6% of anxiety symptoms, 25% of depressive symptoms, and 11% of PTSD symptoms 2 months after ICU discharge. In a small study involving 62 family members, PTSD symptoms were highly prevalent (69.4%) 3 months after ICU discharge. In a multicentric study, Milton et al. reported a prevalence of 8% of anxiety symptoms, 15% of depressive symptoms, and 21% of PTSD symptoms among family members 3 months after ICU discharge. In a longitudinal study with measures at 1, 3, 6, and 12 months after ICU admission, an initial high prevalence of PTSD symptoms (36.3%) decreased over time (24.5%, 21.5%) but increase in the last evaluation (23.6%). Another longitudinal study that involved 221 family caregivers found high levels of PTSD symptoms in 54% of the sample with a trend to reduction during the first 6 months after ICU discharge.

During the current COVID-19 pandemic, Azoulay et al. reported a higher prevalence of anxiety (41% vs 34%), depressive (31% vs 18%), and PTSD (35% vs 19%) symptoms were observed 3 months after ICU discharge among family members of COVID-19 patients, compared to their non-COVID-19 counterparts. In another multicentric study, anxiety, depressive, and PTSD symptoms were experienced at 3- and 12-months post ICU discharge by 31.6% - 29%, 28.3% - 22.8%, and 29.6% - 20.2% of family members of COVID-19 survivors respectively. Overall, the variability in the prevalence of PICS-F psychological impairments could be attributed to the diversity of questionnaires utilized, cut-off values to

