### **PICS-F Physical & Cognitive Impairments**

Compared to PICS-F impairments, physical impairments among family members of ICU survivors have received little attention. Among family members of former ICU ventilated patients, a significant decline in physical health was reported 6 months after hospital discharge. Similarly, clinically significant fatigue was observed in 43%-53% of ICU family members 4 months after hospital discharge. Likewise, these caregivers reported a worsening in depressive symptoms, health risk behaviors, burden, and sleep quality. In the study of Fumis et al., family members showed a decline in physical health 1 month after ICU discharge with a return to baseline levels at 3 months. Other studies have shown mixed results with a small trend to minimal changes in the physical health of family members of ICU survivors.

Although cognitive impairment is common among ICU survivors and ranges from 30% to 80% after hospital discharge, studies exploring the potential impact of critical illness on family members' cognitive function are missing. Significant cognitive impairment is unlikely to be prevalent among family members during ICU admission since they must assume a surrogate decision-making role and frequently communicate with the ICU team. Furthermore, after hospital discharge caregiving tasks are unlikely to be assumed by a relative with relevant impairment in cognition. However, chronic exposure to psychological stress is associated with poorer cognitive function and an accelerated cognitive decline. Considering the high prevalence of psychological impairments among family members of ICU survivors, some form of cognitive impairment may be present, particularly in older family members of ICU survivors.

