### Theoretical Framework

To provide a conceptual organization of the current and potential variables that may be influencing PICS-F impairments, this study will employ an adapted version of the *Pearlin's Caregiver Stress Model* (CSM). In brief, the CSM aims to explain the occurrence of negative outcomes among caregivers (e.g., depression, anxiety, cognitive disturbances, etc.) based on the interaction of the background and contextual factors (family member and patient-related), primary stressors (objective and subjective indicators), and secondary strains (role and intrapsychic). Besides, the relationships between the CSM elements are mediated by psychosocial resources (coping or social support).

In this study, the negative outcomes will be PICS-F impairments (psychological, physical, or cognitive) that are influenced by contextual factors and primary stressors (psychological, physical, and cognitive) experienced by family members during ICU admission/stay and after hospital discharge. Then, secondary stressors can contribute to PICS-F impairments either during the ICU stay (family satisfaction) or after hospital discharge (caregiver burden). In both scenarios, psychosocial resources (social support and resilience) may buffer the primary stressors, secondary stressors, and outcomes. Figure 1 presents the proposed modified version of the CSM model for PICS-F impairments for this study.

[figure not shown]

**Figure 1.** Caregiving Stress Model adapted to Post Intensive Care Syndrome – Family impairments.

**Research questions:** The research questions that will guide the study are: In a sample of family members of ICU survivors of a public hospital in Chile:

- 1) what is the incidence rate of each PICS-F impairment at three and six months after hospital discharge?
- 2) what are the contextual factors, primary stressors, secondary stress, and psychosocial resources associated with each PICS-F impairment at three and six months after hospital discharge?
- 3) If family satisfaction or caregiver burden is associated with PICS-F impairments, to what extent do they contribute to these outcomes at three and six months after hospital discharge?

**Objective:** The aim of this study is two-fold, one cross-sectional and one longitudinal aim.

(1) To determine the incidence of each PICS-F impairment (psychological, physical, and cognitive) among family members of ICU survivors of a public hospital in Chile.

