The incidence of each PICS-F impairments (psychological, physical, and cognitive) at T3 and T4, will be determined by classifying subjects according to the proposed cut-off scores. The number of subjects showing a given PICS-F impairment will be divided by the total number of subjects at the specific point of the study. Then, to analyze factors associated with PICS-F impairments, bivariate and multivariate analyses will be conducted. Cross-sectionally, Chi-square or Fisher's exact test will be applied in case of analyzing two or more categorical variables. In the case of two continuous numerical variables, Pearson or Spearman correlation test will be used. If one dependent variable is continuous normally distributed and the independent variable is categorical, then a t-test (two groups) or ANOVA test (three or more groups) will be applied; if the dependent variable is non-normally distributed, Mann-Whitney U test (two groups) or Kruskal-Wallis test (three or more groups) will be applied. Bivariate analyses, along with factors identified in the literature, will help to identify potential independent variables for multivariate models.

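### The sample size is planned on 20% PTSD symptoms, which matches only the cited study's 12-month rate; at its 3-month rate of 29.6%, the planned 175 evaluable give ±5.7 points, not ±5

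*Protocol*

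**What the plan says.** The Sample Size paragraph (Methods, after Table 1) sets "alpha = 5%, a beta = 80%, and precision of estimate = 5" per cent. Because few studies use the same questionnaires, it adopts "a 20% incidence of PTSD symptoms reported in a study utilizing an IES-6" ≥ 1.75, citing reference 25. It gives no time point for that rate. The single-proportion formula leads to 247, a finite-population step with N = 600 to 175, and an allowance of 40% losses to 292 enrolled.

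The background section on psychological impairments summarises the same reference 25, a multicentre study: "PTSD symptoms were experienced at 3- and 12-months post ICU discharge by 31.6% - 29%, 28.3% - 22.8%, and 29.6% - 20.2% of family members". For PTSD symptoms this means 29.6% at 3 months and 20.2% at 12 months.

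The first research question asks "what is the incidence rate of each PICS-F impairment at three and six months after hospital discharge". The Statistical analyses section says that the number with each impairment "will be divided by the total number of subjects at the specific point of the study". On the physical domain, the background states that "clinically significant fatigue was observed in 43%-53% of ICU family members 4 months after hospital discharge". That figure comes from reference 28, which the protocol also cites for its fatigue cut-off.

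**The concern.** The planning rate agrees with only one of the two PTSD rates that the protocol reports from its chosen source, and that one belongs to 12 months. The study has no 12-month visit. Its first outcome visit is at 3 months, where the same source gives a rate almost half as high again (29.6 / 20.2 = 1.47).

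The variance of a proportion, P(1−P), rises as P moves from 20% towards 50%, so a low planning value makes the expected confidence interval too narrow. Estimating the incidence of each impairment is the first of the study's two objectives, and the 5-point precision is the only justification given for its size. If the precision does not hold at plausible rates, readers are told to expect tighter estimates than the design supports. The same applies to fatigue, whose quoted rate lies close to 50%.

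**Working it through.** **Inputs.** From the Sample Size paragraph: Z = 1.96 (95%), e = 0.05, P = 0.20, N = 600, losses 40%. From the background: 29.6% and 20.2% (PTSD symptoms, reference 25, at 3 and 12 months) and 43–53% (fatigue at 4 months). The stated beta does not enter the formula.

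**The plan's own figures.**
- Initial size: n0 = Z²P(1−P)/e² = 3.8416 × 0.16 / 0.0025 = 245.9. The plan prints 247. P = 0.202 gives 247.7, which truncates to 247. This is consistent with the 12-month source but does not prove it.
- Finite population: 600 × 247 / (600 + 247) = 174.97, so 175.
- Losses: 175 / 0.60 = 291.7, so 292.

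The chain reproduces to within rounding.

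**Half-width with the plan's correction.** The half-width consistent with the plan's adjustment is 1.96 × √[P(1−P)(1/n − 1/600)]. For n = 175 the bracket is 1/175 − 1/600 = 0.0040476.
- P = 0.20: 1.96 × √(0.1600 × 0.0040476) = 4.99 points
- P = 0.202: 5.01 points
- P = 0.296: 1.96 × √(0.2084 × 0.0040476) = 5.69 points
- P = 0.43: 6.17 points
- P = 0.53: 6.22 points

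Setting the half-width to 0.05 gives P(1−P) = (0.05/1.96)² / 0.0040476 = 0.1608, hence P = 0.201. Among rates below one half, ±5 therefore holds only up to about 20%.

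**Six months.** The protocol gives no 6-month figure from reference 25. If the rate lies between 20.2% and 29.6%, the half-width lies between ±5.0 and ±5.7.

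**Half-width without the correction**, 1.96 × √[P(1−P)/175]: 5.9 points at 20%, 6.8 at 29.6%, and 7.4 near 50%.

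**Size needed for ±5 at 29.6% under the plan's steps.** n0 = 3.8416 × 0.2084 / 0.0025 = 320.2, so 321. Then 600 × 321 / 921 = 209.1, so 210 evaluable, and 210 / 0.60 = 350 enrolled. As a check, n = 210 gives 1.96 × √[0.2084 × (1/210 − 1/600)] = 4.98 points.

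**The case against.** The strongest reply is that 29.6% is not the right rate either. It comes from families of COVID-19 survivors, whereas this is a general ICU with COVID-19 as a covariate. The Sample Size paragraph itself sets aside 2021 admissions as pandemic-driven. The same background section gives other 3-month PTSD rates: 19% in non-COVID families, 21% in a multicentre study, and 24.5% in a longitudinal study that counts from ICU admission and gives 21.5% at 6 months. At n = 175 with the correction, 19% to 24.5% gives ±4.9 to ±5.4. This stands as a limit: 29.6% is one planning value, not a known rate. It does not rescue the 20%, because the sponsor chose this source for its IES-6 cut-off, both of its rates come from the same families, and the section also reports higher 3-month rates (35%, 69.4%).

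Three stronger readings are tempting and are not supported.
- **That ±5 is certain to be missed at 3 months.** The 40% loss is not split by visit. If about 210 of the 292 respond at 3 months (a loss of 82/292 = 28%), ±5 still holds at 29.6% with the correction.
- **That a shortfall at 6 months is documented.** It is inferred from the 3- and 12-month values.
- **That the planning rate alone moves the precision to ±6.8 or ±7.4.** Those figures also drop the finite-population correction. Dropping it at P = 20% already moves ±4.99 to ±5.93, which is 0.94 of the 1.77 points between 4.99 and 6.76. Whether the correction is appropriate is a separate question.

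It is also fair to say that sizing on one outcome is common, that the study is exploratory, and that the protocol does not expressly promise 5 points for every domain. But the first objective covers each impairment equally, and no other precision is given.

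**Conclusion.** The point holds as a fault in a planning input, not in the arithmetic. The 20% matches the cited study's 12-month rate, no reason is given for using it, and the study measures at 3 and 6 months. Under the plan's own method and its 175 evaluable, the expected half-width is ±5.7 rather than ±5.0 at the cited 3-month rate, and about ±6.2 for fatigue at the quoted range. The 6-month range of ±5.0 to ±5.7 rests on the assumption that the rate lies between the two reported values.

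The excess is moderate: 0.7 points for PTSD symptoms and about 1.2 for fatigue. It depends on three things: only 175 respondents at the visit in question, the correction with N = 600, and rates from the cited studies carrying over to this hospital. It does not threaten the study's feasibility, but the stated precision should be corrected.

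**What to change.** Keep 292 enrolled and rewrite the Sample Size paragraph as follows.
- State the time point to which the 20% belongs and, if it is kept, why it applies at 3 and 6 months.
- Replace the single 5% precision with expected 95% half-widths for 175 evaluable over the plausible range. With the plan's correction these are ±5.0 to ±5.7 for PTSD symptoms at about 20% to 30%, and about ±6.2 for fatigue at 43% to 53%.
- State one treatment of the finite-population correction and apply it throughout. Without it, the figures are ±5.9 at 20%, ±6.8 at 29.6% and ±7.4 near 50%.
- Mark the 6-month range as an assumption.
- Note that ±5 at 29.6% would need about 210 respondents under the plan's correction.

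The cost is one rewritten paragraph and a less favourable stated precision. No extra participants are needed.
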